### Follow‑up assessments

#### Primary outcome

The dose‑limiting toxicity (DLT) window is defined as Day 1 (first dose of sulfasalazine) through 30 days after the final sulfasalazine dose and gamma knife treatment on Day 3 during which adverse events will be recorded continuously. Adverse events will be graded from 1 to 5 according to Common Terminology Criteria for Adverse Events (CTCAE) version 4.0 [19,20]. For each AE, investigators will assign attribution using standard categories (unrelated, unlikely, possibly, probably, or definitely) to determine the causal relationship to sulfasalazine and GKRS. DLT is defined as any CTCAE v4.0 grade ≥ 3 adverse event occurring within this window, assessed by the investigator as at least possibly related to trial intervention. Adverse events considered to be clearly attributable to expected disease progression or pre-planned hospitalization admission (ie, elective or scheduled surgery arranged prior to the start of treatment) will not be reported as DLT. Similarly, treatment‑related effects expected following GKRS (e.g. pseudoprogression or increased peritumoral edema) and events listed in the sulfasalazine SmPC are not considered “unexpected” and are only classified as Suspected Unexpected Serious Adverse Reactions (SUSAR) if more severe in intensity or more frequent than anticipated.

Safety monitoring includes daily clinical evaluations of vital signs and laboratory testing (hematology, renal/hepatic function, electrolytes, C‑reactive protein, and urine analysis) during the 5-day hospitalization (Day 0–4) in conjunction with the 3-day intervention period (Day 1–3) and at outpatient follow‑up visits at 1, 2, and 4 weeks. MRI will be performed on Day 4 and at 4 weeks to detect early edema and other acute treatment‑related changes. The 4‑week visit will also include [¹¹C]methionine PET. Participant‑reported outcomes during the safety monitoring period will be collected using the FACT‑Br questionnaire at Day 0, Day 4, and weeks 1, 2, and 4. KPS will be assessed at the same timepoints.

Dose escalation follows the 3 + 3 design and proceeds only if no participant experiences a treatment‑related CTCAE v4.0 ≥ 3 adverse event. If one participant experiences a grade ≥ 3 event, the cohort will be expanded to six participants. The maximum tolerated dose (MTD) is defined as the dose preceding that at which 2 of 3 or 2 of 6 patients experience a grade 3 or higher adverse event within the DLT-window.

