#### Imaging methods

Baseline MRI, [¹¹C]methionine PET, and GSH‑edited MRS are performed at baseline before the first sulfasalazine dose. On Day 3, GSH‑edited MRS is acquired in the morning (approximately 09:00), after the third sulfasalazine dose (administered at approximately 07:00) but prior to GKRS (scheduled at around 12:00–14:00). This timing captures the pharmacodynamic effect of sulfasalazine immediately before irradiation. On Day 4, GSH‑edited MRS is repeated approximately 24 hours after GKRS to quantify post‑treatment changes in glutathione levels following three days of sulfasalazine exposure and single‑session radiosurgery. A full MRI ± [¹¹C]methionine PET ± GSH‑edited MRS assessment is performed at the 1‑month follow‑up visit to evaluate longer‑term metabolic and structural changes, including contrast enhancement, tumor size, and glutathione dynamics.

Subsequent MRI scans (T1 with and without contrast, T2, and FLAIR) are conducted at 3, 6, 9, and 12 months. PET imaging is repeated only when clinically indicated, such as in cases of suspected pseudoprogression.

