GSH‑edited MRS is acquired on a 3T Siemens Biograph mMR system using a MEGA‑PRESS sequence with voxels located in the tumor (nominally 27 mL, with placement tailored to maximize coverage of the individual tumor) and healthy tissue (27 mL voxel in the midline anterior cingulate cortex (ACC), adjusted if necessary to avoid intersection with the tumor volume). Similar positioning will be maintained across visits for each individual. With tumor location and size varying between patients, the MRS voxel is placed judiciously on a per-individual basis to maximize intersection with (GD-enhancing) tumor regions, without extending into the ventricles or non-brain regions. Given the comparatively large volume needed for GSH measurement, voxels typically also overlap with smaller portions of the necrotic/non-enhancing core, peritumoral oedema and healthy tissue. Since the behavior of MRS-measured signals (e.g., decay rates for the metabolite and water reference signals) in the different regions is not well defined, there is currently no meaningful way to adjust for this numerically. Importantly, similar placement is maintained across return visits, so these «partial volume» effects are unlikely to substantially impact longitudinal analysis. Healthy reference voxels are placed medially in the ACC, with minor adjustments (slight shifts) in cases where the nominal placement would have intersected with the tumor volume. All MRS data are analyzed through a common pipeline (Gannet 3.3.2), with configuration adjusted (for the entire dataset) to accommodate factors associated with tumor spectra: most notably, spectral alignment is disabled, as this has been found to function poorly in the presence of extremely strong lipid signals and weak (or absent) signals from typical reference metabolites (NAA, Cr). This is outlined, along with quality control criteria and outcomes for the reconstructed spectra, in the MRSinMRS Table 1[23]^,^ [24].

**Table 1 tbl0001:** An MRSinMRS1 checklist for the Phase I Trial Combining Sulfasalazine and Gamma Knife Radiosurgery for Recurrent Glioblastoma. Protocol Identification Number: SAS-GKRS-TRIAL-01, EUDRACT Number: 2019–002,110-40.

Site (name or number)	Haukeland University Hospital

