**3. Data analysis methods and outputs**	
a. Analysis software	Gannet 3.3.2
b. Processing steps deviating from quoted reference or product	Spectral alignment disabled to improve reliability in the presence of extremely strong lipid signal and potentially weak/absent major reference peaks
c. Output measure (e.g. absolute concentration, institutional units, ratio), processing steps deviating from quoted reference or product	Water-referenced estimates for GSH, *without* adjustment for voxel tissue content (traditional segmentation and assumed relaxation rates not suitable in tumor context)
d. Quantification references and assumptions, fitting model assumptions	N/A

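### Similar voxel placement supports the baseline-to-Day 3 GSH comparison, but it does not assure the Day 4 and 1-month comparisons, because voxel content and water signal may change after GKRS

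*Protocol article*

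**What the plan says.** **Voxel content.** Imaging methods describes a tumor voxel of nominally 27 mL and accepts that it is mixed: "voxels typically also overlap with smaller portions of the necrotic/non-enhancing core, peritumoral oedema and healthy tissue". Because signal behavior in these tissues, such as "decay rates for the metabolite and water reference signals", is not well characterized, the section says "there is currently no meaningful way to adjust for this numerically". It then concludes: "Importantly, similar placement is maintained across return visits, so these «partial volume» effects are unlikely to substantially impact longitudinal analysis".

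**Output measure.** Table 1, item 3 (Data analysis methods and outputs) gives "Water-referenced estimates for GSH, *without* adjustment for voxel tissue content".

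**Timing.** MRS is taken at baseline, on Day 3 after the third dose but before GKRS, on Day 4 about 24 hours after GKRS, and at 1 month.

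**Expected change.** The Primary outcome section says "MRI will be performed on Day 4 and at 4 weeks to detect early edema" and names pseudoprogression and increased peritumoral edema as expected effects of GKRS. Imaging methods says the 1-month visit evaluates "metabolic and structural changes, including contrast enhancement, tumor size, and glutathione dynamics". Limitations accepts that edema and pseudoprogression may confound early post-treatment imaging, metabolic readings included.

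**Model.** Data management and analysis gives the fixed effects for GSH as region (tumor or normal-appearing brain), time relative to baseline, and their interaction. Secondary endpoints are described as descriptive and of limited power.

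**The concern.** A voxel in the same position cancels only those partial-volume effects that stay constant between visits. If edema spreads into the voxel, or the lesion grows, shrinks or becomes necrotic, the tissue mix changes even with perfect repositioning. The water signal in the denominator can change too. Neither is adjusted for, and the protocol says that no valid numerical adjustment exists.

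The region-by-time term does not protect against this. The reference voxel lies in the anterior cingulate cortex and is shifted to avoid the tumor. A change confined to the tumor voxel therefore falls on the interaction that would be read as tumor-specific GSH change.

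The stake is the mechanistic claim. The Specifications table and Method validation both present GSH-edited MRS as evidence of mechanism. With the reassurance left as it stands, a Day 4 or 1-month fall or rebound could be read as a biochemical effect when part of it is structural.

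**Working it through.** The protocol gives no effect size, power or bias figure for GSH, so there is nothing to reproduce. The check uses its geometry together with stated assumptions.

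**1. Share of the voxel occupied by tumor.** Inputs: lesion at most 3 cm and 15 cm³ (Inclusion and exclusion criteria); voxel nominally 27 mL (Imaging methods; Table 1 allows some individual adaptation).

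- 3 cm sphere: (4/3) × π × 1.5³ = 14.1 mL; 14.1/27 = 52%
- 15 mL: 15/27 = 56%
- 5 mL: 5/27 = 19%
- 1 mL: 1/27 = 4%

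So at the nominal voxel size at least 44% lies outside the lesion, and 81% does for a 5 mL lesion. There is ample room for the mix to shift.

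**2. Volume route.** Hold GSH constant within each tissue. Let f be the tumor share and r the ratio of tumor to surrounding GSH (assumed 0.5, 1.5 or 2.0). Then

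apparent GSH ∝ f·r + (1 − f).

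Example for a 15 mL lesion halving, r = 2: 1.556 before, 1.278 after; 1.278/1.556 − 1 = −17.9%. With r = 0.5: 0.722 to 0.861, or +19.2%.

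| Lesion | Volume change | r = 0.5 | r = 1.5 | r = 2.0 |
|---|---|---|---|---|
| 15 mL | −50% | +19.2% | −10.9% | −17.9% |
| 15 mL | −25% | +9.6% | −5.4% | −8.9% |
| 5 mL | −50% | +5.1% | −4.2% | −7.8% |
| 5 mL | −25% | +2.6% | −2.1% | −3.9% |
| 1 mL | −50% | +0.9% | −0.9% | −1.8% |

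Growth of the same size reverses the signs. The direction depends on r, which the protocol does not give.

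**3. Water route.** Let a fraction e of the voxel become edematous, with water T2 rising from an assumed 80 ms to 100-160 ms. TE is 80 ms (Table 1), and the water reference is assumed to be acquired at the same TE. The water signal in that fraction is multiplied by k = exp(−80/T2)/exp(−80/80), which is 1.221 at 100 ms and 1.649 at 160 ms. With the GSH signal unchanged,

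apparent change = 1/(1 − e + e·k) − 1.

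| New edema, share of voxel | T2 effect only | Also 10% more water |
|---|---|---|
| 5% | −1.1% to −3.1% | −1.7% to −3.9% |
| 10% | −2.2% to −6.1% | −3.3% to −7.5% |
| 20% | −4.2% to −11.5% | −6.4% to −14.0% |
| 40% | −8.1% to −20.6% | −12.1% to −24.6% |

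Under these assumptions new edema always lowers apparent GSH, which is the direction hypothesized for sulfasalazine.

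**4. What the model does with it.** Let the observed tumor ratio to baseline be the true ratio times an artifact a. On the log scale the region-by-time contrast is the true contrast plus log(a, tumor) − log(a, reference). If the reference voxel is unaffected, its a is 1, and the whole of log(a, tumor) stays in the contrast.

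**5. Which visit is exposed.**

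- *Baseline to Day 3:* no irradiation has occurred, so neither route is opened by GKRS.
- *Day 4:* about 24 hours after GKRS, so the plausible route is edema or water signal. A pre-procedural steroid dose is permitted when edema is present (Concomitant medications and supportive care). The documents give no basis for sizing its effect on water signal.
- *1 month:* both routes are open, and this is where volume change mainly matters.

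**The case against.** The strongest reply is that the protocol is already candid. It discloses the mixed voxel, the undefined decay rates, the lack of a numerical correction and the unadjusted water reference, and Limitations concedes confounding of early imaging in general terms. Imaging methods ties Day 3 to the drug effect and does not attribute the later scans to sulfasalazine alone. The endpoint is secondary and descriptive. All of this stands. What remains is that the sentence on placement covers every return visit without qualification and sits uneasily with Limitations.

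The size can also be challenged. The largest volume figures need a lesion at the eligibility ceiling to halve within a month, at an assumed GSH ratio, and their sign depends on that ratio. Justification for prescription dose cites less than 10% radiographic edema in a 77-patient cohort at a median of 12 Gy. This stands as a reason for restraint. However, that figure is presented as experience with GKRS, whereas this trial adds a putative radiosensitizer, and it does not speak to change in lesion size.

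A reader might infer more than the documents support:

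- *That the protocol claims fixed placement removes partial-volume effects.* It says similar placement makes a substantial impact unlikely.
- *That Day 4 and 1-month GSH change is confounded.* No document gives the size of structural change, so only the possibility is supported.
- *That edema is forecast as frequent.* The list of expected effects appears in the context of classifying unexpected serious reactions and states no frequency.
- *That no other model term could be used.* The text says what the fixed effects will include, and an analysis plan that is not shown may add sensitivity terms.

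**Conclusion.** The point holds in a limited form. The reassurance is reasonable for baseline versus Day 3 and for partial-volume effects that stay constant over time. It is not assured for Day 4 or 1 month, where the protocol itself looks for the changes that would break it.

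The possible artifact is about 0-3% for a small, stable lesion with little edema. It reaches about 20% for a 15 mL lesion that halves or for new edema in 40% of the voxel, and about 25% in the latter case if water content also rises by 10%. These figures rest on assumed GSH ratios, volume changes, edema extent, water T2 and water content, on the nominal voxel size, and on a water reference acquired at TE 80 ms. They show what could happen and do not predict what will.

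The Day 3 contrast is not touched by GKRS effects. MTD determination and the recommended phase II dose are unaffected. The matter is worth correcting because it changes what the later GSH results can support.

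**What to change.** 1. In Imaging methods, restrict the sentence on similar placement to the baseline-to-Day 3 contrast, and reconcile it with the statement on edema and pseudoprogression in Limitations.
2. Name baseline to Day 3 as the contrast for the effect of sulfasalazine on GSH. State that Day 4 and 1-month GSH values are descriptive and possibly confounded by structural change.
3. Beside the GSH values, report by visit the geometric fractions of the tumor voxel that are enhancing, non-enhancing or necrotic, and FLAIR-abnormal. Purely geometric fractions need no relaxation model, so the protocol's objection to numerical adjustment does not apply. Contrast-enhanced T1, T2 and FLAIR are already scheduled on Day 4 and at 4 weeks, and MRI is done at baseline (its sequences are not listed). The stereotactic planning MRI could give the enhancing fraction close to the Day 3 scan.
4. Report the unsuppressed water amplitude by visit. The water-referenced output already requires it.
5. Do not rely on a model adjusted for enhancing fraction. That fraction is itself a post-treatment response, is near zero by design in the reference voxel, does not address water signal, and would be estimated imprecisely in 12-24 patients. If used at all, it should be exploratory and confined to the tumor voxel.

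The cost is offline co-registration of planned images and some wording, with no new scans. The downside is that claims from Day 4 and 1-month GSH become weaker.

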**1. Hardware**	
a. Field strength [T]	3 T
b. Manufacturer	Siemens
c. Model (software version if available)	Biograph mMR, VE11P
d. RF coils: nuclei (transmit/receive), number of channels, type, body part	mMR head/neck matrix coil (1H receive), 12/20 channels active
e. Additional hardware	N/A

**2. Acquisition**	
a. Pulse sequence	MEGA-PRESS (GSH editing, Universal implementation)
b. Volume of interest (VOI) locations	Subject-specific intra-tumoral and contralateral healthy tissue
c. Nominal VOI size [cm3, mm3]	Nominally 27 mL (30 × 30 × 30 mm^3^), some individual adaption
d. Repetition time (T_R_), echo time (T_E_) [ms, s]	T_R_ = 2000 ms, T_E_ = 80 ms
e. Total number of excitations or acquisitions per spectrumIn time series for kinetic studies i. Number of averaged spectra (NA) per time point ii. Averaging method (e.g. block-wise or moving average) iii. Total number of spectra (acquired/in time series)	256 transients total, alternating edit-ON/-OFF
f. Additional sequence parameters (spectral width in Hz, number of spectral points, frequency offsets) If STEAM:, mixing time (T_M_) If MRSI: 2D or 3D, FOV in all directions, matrix size, acceleration factors, sampling method	Spectral width 4000 Hz, 4096 data points 15 ms editing pulses at 4·56 ppm (edit-ON) and 7·5 ppm (edit-OFF)
g. Water suppression method	CHESS
h. Shimming method, reference peak, and thresholds for “acceptance of shim” chosen	3D-DESS (or FASTESTMAP)
i. Triggering or motion correction method (respiratory, peripheral, cardiac triggering, incl. device used and delays)	N/A

**3. Data analysis methods and outputs**	
a. Analysis software	Gannet 3.3.2
b. Processing steps deviating from quoted reference or product	Spectral alignment disabled to improve reliability in the presence of extremely strong lipid signal and potentially weak/absent major reference peaks
c. Output measure (e.g. absolute concentration, institutional units, ratio), processing steps deviating from quoted reference or product	Water-referenced estimates for GSH, *without* adjustment for voxel tissue content (traditional segmentation and assumed relaxation rates not suitable in tumor context)
d. Quantification references and assumptions, fitting model assumptions	N/A

**4. Data quality**	
a. Reported variables (SNR, linewidth (with reference peaks))	SNR GSH 8·05 [3·03,12·9] (healthy), 4·16 [2·.25,8·83] (lesion) SNR NAA 152 [99·7·247] (healthy), 77·4 [29·.3·153] (lesion) SNR Cr 130 [84·4·215] (healthy), 63·1 [20·9114] (lesion) FWHM GSH 10·1 [5·46,14·7] (healthy), 11·8 [5·15,23·11] (lesion) FWHM NAA 11·6 [8·66,21·67] (healthy) 18·1 [11·4,26·7] (lesion) FWHM Cr 10·2 [7·90,16·8] (healthy), 16·1 [10·2,22·8] (lesion) Reported as median [95% confidence interval]; FWHM in Hz
b. Data exclusion criteria	FWHM GSH > 30 Hz; SNR GSH < 2
c. Quality measures of postprocessing model fitting (e.g. CRLB, goodness of fit, SD of residual)	FitError GSH > 50%; any parameter estimate < 0 Extreme outliers (> 3 x median absolute deviation evaluated from baseline acquisitions (timepoint D1) on healthy side)

[¹¹C]methionine PET is performed on the integrated 3 T PET/MRI system [¹¹C]methionine is administered intravenously according to institutional weight‑based protocols, and imaging begins after a tightly controlled uptake time (10–20 min) to account for the short half‑life of carbon‑11 (20.3 min). PET data are reconstructed with MR‑based attenuation correction and standardized OASIS‑based processing. Volumes of interest (VOIs) are placed on co‑registered PET/MR images, with the lesion VOI centered on the region of highest methionine uptake while excluding necrotic or hemorrhagic tissue, and the reference VOI placed in contralateral normal‑appearing cortex or white matter. SUVmax and SUVmean are extracted, and tumor‑to‑normal (T/N) ratios are calculated using the contralateral reference region. All PET analyses are performed centrally by an experienced nuclear medicine physicist/radiologist using the prespecified OASIS pipeline to ensure reproducibility. PET‑RANO 1.0 criteria [25] are applied for metabolic response categorization.

#### Radiosurgery methods

GKRS is delivered in a single session using a Leksell stereotactic frame and contrast‑enhanced stereotactic MRI for target definition. The target is defined as the contrast‑enhancing tumor volume on T1‑weighted post‑contrast MRI with 1-mm slice thickness, with no additional margin. A prescription dose of 12 Gy is delivered to all lesions.

The planning goal is to use the 50% isodose line for optimal conformity and steep dose fall‑off. However, for very small lesions (≤ 1 cm³), a higher prescription isodose line (50–90%) may be selected to improve conformality and to minimize the 12‑Gy volume outside the target.

Plan quality is evaluated using standard GKRS metrics (tumor volume, prescription isodose, minimum and maximum dose, the 12‑Gy volume outside the target (V₁₂Gy), target coverage ratio, conformity index, selectivity index, and gradient index, dose rate) with planning objectives of a conformity ratio close to 1.0 (<1.05), selectivity >0.75, and a gradient index ≤3.0 (PCI <90%). These serve as guiding targets rather than strict constraints, with highest priority placed on achieving optimal target coverage while minimizing V₁₂Gy.

Normal‑tissue constraints follow institutional practice including brainstem V₁₂Gy < 1 ml, maximum dose to the optic apparatus < 8 Gy; and cochlear maximum dose < 4 Gy where applicable. Prior radiotherapy is incorporated into planning by restricting the treated volume to ≤ 15 cm³ and minimizing V₁₂Gy to normal brain. A fixed 12 Gy salvage dose is used independent of time since prior radiotherapy to minimize variability across cohorts. Patients previously treated with repeat fractionated reirradiation or GKRS for recurrence at the same target are excluded.

#### Justification for prescription dose

In the reirradiation setting, patients have already received 60 Gy to normal brain, creating a narrow therapeutic window. A 12 Gy prescription dose is consistent with our institutional practice and published experience. In a cohort of 77 rGBM patients treated with a median margin dose of 12 Gy (range 8–20 Gy) the median OS was 12 months, PFS 6 months, with <10% radiographic edema, and no treatment‑related neurological toxicity or radionecrosis. Importantly, outcomes did not improve with doses exceeding 12 Gy[8].

The 12 Gy isodose volume (V12Gy) is a recognized predictor of adverse radiation effects, and radionecrosis risk increases steeply as V12Gy expands. Even small increases in prescription dose or target volume can markedly increase toxicity without demonstrating a clear gain in OS. This is illustrated by Koga et al., where adding a 0.5 −1 cm margin to a 20 Gy plan did not improve OS but increased the rate of radionecrosis from 6.5% to 29%[26]. While Bunevicius et al. (n = 96) found that doses >15 Gy and treatment volumes ≤5 cm³ predicted longer OS in univariate analysis, only volume remained significant after multivariate adjustment, highlighting the dominance of the dose–volume relationship[27]. Several studies, however, illustrate the dose‑toxicity relationship as well. Imber et al. (n = 174, grade 4 glioma) reported a 13% incidence of radiation necrosis requiring surgery using a 16 Gy prescription dose, with a median OS of 10.6 months and prescription doses >15.5 Gy emerging as a positive predictor of OS[28]. In another study employing a 20 Gy prescription dose, the radionecrosis rate approached 40%, with 23% of patients requiring resection, while OS (11.3 months) remained similar to that seen in lower‑dose series[10]. Conversely, lowering the prescription dose below 12 Gy appeared to be safer, although not more effective, as reflected in the Vienna experience (median 10 Gy), which reported an OS of 9.6 months with no treatment‑related toxicity[29].

Although several retrospective studies have suggested that higher prescription doses (>14- 16 Gy) may be associated with improved PFS or OS, the OS in these trials seldom exceeds 12 months despite dose escalation. Consequently, dose–response relationships in the SRS literature must be interpreted with caution, as they are heavily confounded by tumor volume, tumor grade, and study heterogeneity. Most published reports are small, retrospective, single‑institution cohorts that mix WHO grade 3 and grade 4 gliomas, often lack IDH classification, combine SRS boost at diagnosis with SRS for recurrence, use different radiosurgical platforms and fractionation schemes, and apply prescription doses ranging from 10 to 20 Gy with variable target margins. Reported tumor volumes span from 0.01 to 99 cm³, further complicating assessment of any true dose–response relationship for GKRS in IDH‑wildtype recurrent glioblastoma following standard chemoradiation with the Stupp regimen. The ISRS guidelines recommend a prescription dose of 16 Gy, based on a meta analysis that combines WHO grade 3 and grade 4 gliomas[30]. Because grade 3 gliomas consistently demonstrate substantially longer survival than grade 4 gliomas, this tumor grade heterogeneity further obscures interpretation of dose–response relationships. For example, Dodoo et al. reported a median OS of 31.3 months for grade 3 versus 11.3 months for grade 4 at a 20 Gy prescription dose, with radionecrosis rates of 40%(10).

Taken together, our institutional data supports 12 Gy as a balanced single‑session GKRS dose with comparable survival rates as > 12 Gy studies while minimizing radionecrosis risk in previously irradiated, IDH‑wildtype GBM recurrence.

